### Intervention

All clinics followed the same study protocol. BSHX granules and placebo granules were assigned to different groups for a period of 3 months of treatment. The prescription of placebo is composed of 98% maltodextrin, 2% caramel, and very little bitterant. The BSHX and placebo were manufactured by Jiangyin Tianjiang Pharmaceutical Co. Ltd. (Jiangyin, Jiangsu Province, China) in compliance with China Good Manufacturing Practice standards. Both BSHX and placebo were approved and regulated by the China Food and Drug Administration (FDA) and can be valid for 2 years. The medicines have been widely used in our hospital for many years, and the clinical efficacies were noticeable. Different from other traditional herbs prepared by boiling, it is easier and quicker by dissolving BSHX or placebo (one bag three times a day, 30 g/bag) in water for 30 min. Treatment was taking these medicines after meals three times a day for 3 months. After treatments, medicine packages will be required to return, and compliance will be calculated based on the residual medication. Dosages of Chinese medicines were in accordance with the latest standards of the Chinese Pharmacopoeia (2015 edition). Trial records were confidential and secure.

### Follow-up

All included patients will be re-evaluated at 2, 4, 6, 8, 10, 12, 16, 20, and 24 weeks’ follow-ups. Wherever in-person follow-up was not possible, video conferencing or telephone follow-up was carried out.

### Safety assessments

Studied medicine safety testing includes liver and renal function test, blood routine examination, urine routine examination, stool routine examination, and electrocardiogram. These parameters will be obtained both at screening and after treatment, and all samples were tested by the Jiangsu Province Hospital on Integration of Chinese and Western Medicine in China. Standardized protocols exist at the study center regarding the management of known of potential adverse effects. Adverse events related to the intervention will be monitored through review of the patient’s records, participant self-report, and by the clinicians. All adverse events during treatment and follow-up will be recorded and analyzed in detail. If a participant has a serious adverse event and was not safe to continue the trial, the participants were requested to withdraw from the trial. Immediate relevant treatments were provided to those participants, and following up continued until the response was terminated.

### Outcome measures

#### Primary outcome

The primary outcome measurement was the CMS questionnaires. The CMS was translated by Yang Hongyan and others [24]. In clinical practice, the Chinese version of the MENQOL Questionnaire (Table S3 in supplementary materials) has been proven to be highly reliable, effective, and responsive. It is a reasonable and effective tool to comprehensively evaluate the current physical and mental health problems of menopausal women in China [25]. CMS has a total of 29 items, which are divided into 4 dimensions, including vasomotor symptoms (3 items), psychosocial symptoms (7 items), physiological health (16 items), sexual health-related questions (3 items). Differences in this questionnaire are that MENQOL appears not only as symptoms based on the frequency, it also includes the troubles caused by various severity of symptoms degree. Participants will complete the questionnaires before, after the intervention, and follow-up. Items measured and data collection schedule are shown in Table S4 (in supplementary materials).

#### Secondary outcomes

The secondary measurements included serum sex hormone levels, AMH, AFC, and PSV (cm/s). The regulatory effect of tested medicine on hormone balance was monitored by the level of serum sex hormones (FSH, LH, E2). The blood samples of all subjects were taken in the early antral follicular phase before treatment and after the withdrawal of the drug. As an ovario specific growth factor, AMH is an effective and reliable indicator to predict ovarian reserve function [26], and it has no cycle-dependent [27]. AFC is helpful to evaluate the relative accuracy of ovarian reserve function when used in combination with sex hormone detection and can also provide a reference for the formulation of the treatment plan [28]. Transvaginal ultrasound is the best way to observe AFC indicators, which can be accurately evaluated and calculated the number of follicles. Generally, the AFC is measured at the beginning with the early antral follicular stage. Transvaginal ultrasound is performed by an experienced ultrasound expert, and the follicle count of both ovaries with a diameter of 2–10 mm (measured by clinicians rather than automatically calculated) is used to calculate AFC. All subjects underwent vaginal ultrasound examination at the follicular stage before treatment and after drug withdrawal.

### Quality control

The multicenter clinical trial is a complex process, and quality control is a reliable guarantee for this trial. Effective quality control measures were carried out to ensure the quality of the trial and the accuracy of results, completeness, and authenticity of the information. At the same time, the rights and welfare of participants should be guaranteed. Being the authority among research centers, Jiangsu Province Hospital on Integration of Chinese and Western Medicine is in charge of formulating the standard operating procedures (SOPs) training, and visiting each site regularly to guidance the trial, which strictly followed the protocol. The data were collected timely, directly, accurately, and clearly. The recordings were regularly self-checked its accuracy and completeness. Any errors were corrected in accordance with the prescribed methods. Data from case reports were published on the public clinical trial management platform (www.medresman.org) within 6 months after the end of the trial. An independent data safety monitoring committee, which is independent of the sponsor without competing interests, was in charge of data validation.

### Statistical analysis

Data will be analyzed with SPSS V.21 (IBM) by statisticians independent from involved researchers in this study. Efficacy and safety will be evaluated by intention-to-treat (ITT) analysis within the full analysis set (FAS) according to the ITT principle. At the same time, per-protocol (PP) analysis will apply to evaluate data collected from subjects who have completed all steps of the trial protocol. Results of the full analysis set and the per-protocol set will be compared. All prespecified outcomes will analyze in the ITT population because ITT analysis often underestimates the efficacy and was usually conservative. On the contrary, PP analysis overestimates the efficacy and the differences between the two groups. Therefore, this study mainly uses ITT analysis, and PP analysis will be applied if there was a statistical significance. Various assignment methods were used to detect whether the results of different assumptions of missing data are robust. The safety evaluation will be conducted by ITT analysis.

Descriptive analysis will be used for baseline variables including demographic characteristics, medical history, course of disease, treatment history, combined diseases, concomitant medications, vital signs, laboratory tests for safety assessment, and adverse events. Continuous variables will be expressed by mean ± SD; categorical variables will be shown as counts and percentages. Estimates of the adjusted differences in risks are presented with 95% confidence intervals (CIs) of the difference. The comparability of the characteristics between the BSHX and placebo groups will be assessed by using *t*-test for continuous variables with normal distribution, while the non-parametric Mann-Whitney-Wilcoxon test will be used for the comparison of data with non-normal distribution. Specifically, the paired *t*-test will be used to compare the difference of the outcome between preintervention and postintervention in each group and independent t-test will be used to compare the difference between the two groups. Categorical variables will be compared using *Χ*^2^ statistics, while the Fisher exact test will be used when the theoretical frequency is less than 5 in more than 25% of the cells. In order to control the center and baseline effects, covariance analysis will be applied for the intergroup comparison with continuous variables and Cochran-Man-tel-Haenszel test for categorical variables. The differences of CMS scores, levels of FSH, LH, E2, AMH, the AFC, and ovarian PSV (cm/s) at month 0 and month 3 between the BSHX and placebo groups will be compared using an independent *t*-test. A repeated-measures analysis of variance (ANOVA) test with Bonferroni post hoc test will be used to evaluate the changes in CMS scores, levels of FSH, LH, E2, AMH, the AFC, and ovarian PSV (cm/s) and safety assessment measurements throughout the experiment. In all tests, a value of *p* < 0.05 will be considered statistically significant. All statistical analyses will be performed using SPSS V.20.0.

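### Safety is assigned to the ITT population, and the only test named for the laboratory safety measures compares means, which responds poorly to a few marked abnormalities

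*Protocol article*

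**What the plan says.** **Population.** The Statistical analysis section of the protocol article fixes the safety population twice. It first says "Efficacy and safety will be evaluated by intention-to-treat (ITT) analysis within the full analysis set (FAS) according to the ITT principle", and closes the same paragraph with "The safety evaluation will be conducted by ITT analysis". No safety set defined by treatment taken is named. The reason given for preferring ITT is that it tends to understate efficacy and is therefore cautious.

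**Laboratory measures.** Under Safety assessments the tests are "liver and renal function test, blood routine examination, urine routine examination, stool routine examination, and electrocardiogram", and "These parameters will be obtained both at screening and after treatment". The repeated-measures ANOVA with Bonferroni post hoc test in the Statistical analysis section covers the hormone, follicle-count and blood-flow outcomes "and safety assessment measurements throughout the experiment".

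**Other safety provisions.** Safety assessments also says "All adverse events during treatment and follow-up will be recorded and analyzed in detail". The Statistical analysis section lists adverse events and safety laboratory tests under descriptive analysis. It gives continuous data as mean and SD, and says "categorical variables will be shown as counts and percentages", with chi-square or Fisher tests and risk differences with 95% confidence intervals.

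**The concern.** Two stated choices fit safety badly.

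The first is the population. A set chosen because it tends to shrink the apparent treatment effect is cautious when the claim is benefit. When the question is harm, the same shrinkage works in the favourable direction. Women who took nothing add to the denominator and not to treatment-related events, and a woman given the wrong package has her events counted under the other arm.

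The second is the laboratory test. Harm to the liver or kidney, if it occurs, may appear as a few women with large abnormalities and not as a shift of the whole group. A comparison of means is built for the group shift. With two measurements per woman, the Bonferroni step over time has one pair to compare and so adjusts nothing. Results such as urine, stool and ECG findings may be categorical, and an ANOVA does not suit those.

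Safety stands beside effectiveness in the primary objective at the end of the Introduction, so its analysis deserves methods suited to it.

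**Working it through.** The article states no safety event rate or laboratory figure, so there is nothing of its own to reproduce. The check takes each choice in turn.

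**Inputs from the article.** 150 women allocated 1:1, so 75 per arm; safety laboratory tests at two time points; significance at p<0.05; maximum dropout 15%. **Assumed.** The undosed share *u*, and all liver-enzyme (ALT) values.

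**1. Dilution.** If a fraction *u* of an arm is never dosed and has no treatment-related events, the reported rate is *r* × (1 − *u*), where *r* is the rate in treated women. For *r* = 10%:

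| Undosed share *u* | Reported rate |
|---|---|
| 0 | 10.0% |
| 1% | 9.9% |
| 5% | 9.5% |
| 5 of 75 (6.7%) | 7/75 = 9.3% |
| 15% (every planned dropout undosed) | 8.5% |

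The last row is an extreme, because most dropouts in such a trial would have taken some medication. The event count does not change, and equal undosed shares dilute both arms alike.

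**2. What the ANOVA tests.** With two time points, the group-by-time test is the two-sample t-test on change from screening. Suppose *k* of the *n* = 75 BSHX women rise by a very large amount *D*, and all other change is negligible beside it. Then:

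- difference in mean change = *kD/n*
- squared standard error = *D*² × (*k/n*)(1 − *k/n*)/(*n* − 1)
- *t* = √[*k*(*n* − 1)/(*n* − *k*)] = √[74*k*/(75 − *k*)]

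*D* cancels, because the outliers raise the variance along with the mean. The 5% critical value on 148 degrees of freedom is 1.976.

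| *k* | Limiting *t* |
|---|---|
| 1 | 1.00 |
| 2 | 1.42 |
| 3 | 1.76 |
| 4 | 2.04 |
| 5 | 2.30 |

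With one to three women, a more extreme abnormality therefore does not rescue the test.

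**3. Simulation.** Assumed ALT mean 20, SD 8, correlation 0.6 between visits, upper limit of normal (ULN) 40, and 3000 runs per setting. The chance of p<0.05 when *k* of 75 BSHX women are set to the stated multiple of the ULN after treatment is:

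| *k* | 3 × ULN | 5 × ULN | 10 × ULN |
|---|---|---|---|
| 1 | 3% | 1% | 0% |
| 2 | 7% | 3% | 0% |
| 3 | 19% | 15% | 4% |
| 4 | 40% | 51% | 65% |
| 5 | 67% | 90% | 99.8% |

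With no abnormal women the test rejects in about 5% of runs, as it should. A different assumption (lognormal ALT, median 18 U/L, log-SD 0.4, t-test on post-treatment means) gives 0.1% for two women at 400 U/L, 16% for three at 200 and 6% for three at 400.

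**4. Would a test on counts do better?** Fisher's exact test against 0/75 gives p = 0.245 for 3/75, 0.12 for 4/75, 0.058 for 5/75 and 0.028 for 6/75. It also misses few cases. A displayed count does not depend on a p-value. The chance that at least one case occurs among 75 women, and so can be shown, is 1 − 0.98^75 = 78% at a 2% rate and 1 − 0.96^75 = 95% at a 4% rate.

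**The case against.** The strongest reply is that the ANOVA is not the whole safety analysis. Adverse events are collected from records, self-report and clinicians, and categorical data get counts, tests and risk differences. A woman with a very high liver enzyme could be reported as an adverse event and counted. This stands. A reader might infer that serious abnormalities cannot be detected at all, and the article does not support that. It does not say, however, that an abnormal laboratory value becomes an adverse event, and a mean with SD does not show individuals.

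A reader might also infer that a non-significant difference in means will be reported as proof of safety. No sentence in the article says so.

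Dilution is hypothetical. No undosed women or swapped packages are reported, and the article does not say whether the full analysis set keeps women who were never dosed. This also stands, so the effect is conditional and probably small.

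The ANOVA is not invalid with two time points, and its safety clause can be read as covering continuous measures only. With four or five cases it rejects more readily than a Fisher test would. Removing it is therefore a matter of preference.

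Finally, shift tables and abnormality limits usually belong in an analysis plan, which is not shown. Their absence is not the fault raised here. The fault lies in the two methods the article does state.

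**Conclusion.** The point holds in a limited form. The article assigns safety to ITT on a rationale that concerns efficacy, and the one test it names for the laboratory safety measures is insensitive to a few extreme values.

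On the population, the bias is zero if every woman is dosed as allocated. It reaches 15% of the event rate (10% read as 8.5%) only in the extreme where every planned dropout is undosed.

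On the laboratory test, the chance of p<0.05 is roughly 0–19% with one to three markedly abnormal women among 75, and 67–99.8% with five. These figures rest on assumed ALT distributions. The weakness at one to three cases does not depend on them once the abnormalities are very large, as the limiting *t* values show. The finding also takes the two time points under Safety assessments as the full laboratory schedule, since the supplementary schedule table is not shown.

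This is an inexpensive improvement to the safety analysis. It does not affect the efficacy analysis.

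**What to change.** Replace the sentence that assigns safety to ITT with wording such as: *Safety will be analysed in all women who took at least one dose, grouped by the treatment actually received.* Change the earlier sentence that pairs efficacy and safety in the full analysis set to match.

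Make by-arm shift tables from screening to after treatment, and by-arm counts of abnormal laboratory and ECG values, the main laboratory safety summary. The abnormality limits should be set by the investigators before unblinding.

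A comparison of mean change from screening may stay as supportive for continuous measures. Categorical results should go to the counts and the chi-square or Fisher tests that the section already provides.

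The cost is a wording change and a few extra tables, with no new data and no change to sample size or visits.

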**Methods and design:**

We plan to recruit 150 women with POI from four participating hospitals in China. Participants will be randomized in a 1:1 to receive oral BSHX or BSHX placebo. All participants will be treated for 3 months and will be followed up for another 3 month. The primary outcome is questionnaire scores based on the changes in the total symptoms, which is the Chinese version of the Menopause-Specific Quality of Life (CMS) (Nie G, Yang H, Liu J, Zhao C, Wang X, Menopause 24(5):546–554, 2017). CMS will be measured before the intervention, at 3 months and 6 months after randomization for all participants. The other measurements include serum sex hormone levels, anti-Müllerian hormone (AMH) levels, ovarian peak systolic velocity (PSV; cm/s), and antral follicle count (AFC). In this study, the regulatory effects of traditional Chinese medicine on hormones were evaluated by the changes of serum sex hormone levels, which include serum estradiol (E2), luteinizing hormone (LH), and follicle-stimulating hormone (FSH). These indicators will be measured before intervention and at 3 months after randomization.

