### Sample size calculation

Sample size estimation refers to the calculation of the required sample size in order to meet the accuracy and reliability of statistics (the control of type I errors and the guarantee of inspection efficiency) [21]. The sample size of this study was based on the relevant literature reviews and the validity of hypotheses. The main indicator of this study is to detect the difference of the total score (CMS) between the two groups before and after treatment. There is one randomized clinical trial for BSHX in the treatment of POI [13]. However, there is no placebo control group in the clinical trial and the primary outcome measurements were different. Thus, the parameters are not suitable to estimate the sample size of the trial. We referred to other clinical trials of traditional Chinese medicine in the treatment of POI patients [22]. We assumed that BSHX administration would reduce CMS score by 2.9 points and the SD is 7.42 in the study [23]. If a type I error rate of *α* = 0.05, a power of 90 % (type II error rate of *β* = 0.1), then u1 − *α* =1.64, u1 − *β* =1.28. n1 = n2 ≈ 70. During the 3-month treatment period, taking into account the possible protocol violations, and the maximum possible drop-out rate of 15%, we need 148 participants in total to achieve the number of people required for the efficacy analysis. One hundred fifty participants will be recruited for this study, and the following formula was used to estimate the sample size:
$$ n=2\times {\left[\frac{\left({z}_{1-\raisebox{1ex}{$\partial $}\!\left/ \!\raisebox{-1ex}{$2$}\right.}+{z}_{1-\beta}\right)\sigma }{\delta}\right]}^2 $$

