### Randomization and blinding

The randomization sequence is generated by a computer and randomization numbers are hidden in sealed, opaque, and sequentially numbered envelopes, which are properly kept until the end of the trial. Participants will be randomly assigned (1:1) using a computer-generated randomization sequence to receive oral BSHX or BSHX placebo. The statistician who is not involved in recruiting will prepare the randomization list, and the list will not be available to anyone in any center. Researchers who do not participate in the recruitment label the envelopes. Meanwhile the size, color, taste, and shape of the placebo are consistent with the corresponding drugs, and all study groups assigned by different numbers will use the same packages of medicines. All the documents related to the randomization and allocation sequence generation will be kept in a box in a locked cabinet away from the clinical environments. Packages of BSHX and placebo were provided to randomly assigned two groups of women in each hospital’s centers. This is a double-blind trial, in which all researchers and subjects will be blinded for the treatment allocation until the trial is completed. If there is a serious adverse event or an emergency unblinding event, the blind will be immediately broken.

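### Three between-group analyses are named for the hormones, AMH, AFC and PSV with none ranked, and the outcome-specific sentence picks the unadjusted t-test

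*Protocol article*

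**What the plan says.** One paragraph of the Statistical analysis section contains everything the article says about comparing the groups on the secondary outcomes.

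- **Outcome-specific sentence.** "The differences of CMS scores, levels of FSH, LH, E2, AMH, the AFC, and ovarian PSV (cm/s) at month 0 and month 3" are to be compared between BSHX and placebo with an independent t-test. No scale is named. The sentence can mean a test of the month-3 values or a test of the change.
- **Covariance analysis.** A general sentence plans it for intergroup comparisons of continuous variables, to control centre and baseline effects.
- **Repeated-measures ANOVA** with a Bonferroni post hoc test is planned for the same list of outcomes, CMS included.
- **Non-normal data.** In the sentence on comparability of characteristics between the groups, "the non-parametric Mann-Whitney-Wilcoxon test will be used for the comparison of data with non-normal distribution".
- **Threshold.** "In all tests, a value of *p* < 0.05 will be considered statistically significant".

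On timing, the Abstract says of these measurements: "These indicators will be measured before intervention and at 3 months after randomization". CMS, by contrast, is measured before the intervention and at 3 and 6 months.

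**The concern.** Each of the three analyses gives its own estimate and p-value for the same question, and the paragraph does not rank them. An analyst who follows the most specific sentence uses the t-test and so drops the centre and baseline adjustment that the paragraph itself asks for. That gives up precision obtainable from data already collected. An analyst who runs all three has no stated rule for which result to report, and each is judged at 0.05.

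Scale is a second, more conditional matter. Hormone and AMH concentrations are bounded below and may be right-skewed. If so, a few large values weigh heavily in any raw-scale analysis, ANCOVA included. At stake is how sensitive and how credible the secondary results are. The primary CMS conclusion is not part of this point.

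**Working it through.** **Figures in the plan.** No power, SD, correlation or effect is stated for FSH, LH, E2, AMH, AFC or PSV, so there is no figure to reproduce for them. The only sample-size calculation is for CMS (difference 2.9, SD 7.42, 90% power). Its printed two-sided formula gives 2 × [(1.96 + 1.28) × 7.42 / 2.9]², about 138 per arm, not the stated 70. That is a separate matter and nothing below rests on it.

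**Inputs.**
- From the plan: 1:1 allocation, 150 recruited, 15% drop-out, alpha 0.05. This leaves 150 × 0.85 / 2 = 63.75, taken as 64 per arm.
- Assumed: log-normal baseline and month-3 values, log SD 0.3 to 1.0, baseline to month-3 correlation (r) on the log scale 0.5 to 0.7, a multiplicative treatment effect, no centre effect.
- Effect on the log scale = 2.80 × SD × √(2/64) = 0.495 × SD, where 2.80 = 1.96 + 0.84, which gives a two-sided log-scale t-test 80% power. At SD 0.5 this is a ratio of exp(0.247) = 1.28; at SD 1.0 it is exp(0.495) = 1.64.

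**Step 1: baseline adjustment alone, by formula.** On a scale where the data are normal, ANCOVA multiplies the residual variance by 1 − r².
- Unadjusted: Φ(2.80 − 1.96) = Φ(0.84) = 80%.
- r = 0.5: 2.80 / √0.75 = 3.23; Φ(3.23 − 1.96) = Φ(1.27), about 90%.
- r = 0.7: 2.80 / √0.51 = 3.92; Φ(3.92 − 1.96) = Φ(1.96), about 97.5%.

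So the t-test costs about 10 to 17 points with no skew at all.

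**Step 2: simulated power with skew.** Ranges cover both correlations.

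| Analysis | Log SD 0.3-0.5 | Log SD 0.8-1.0 |
|---|---|---|
| Raw t-test, month 3 | 73-77% | 59-68% |
| Raw ANCOVA | 83-96% | 67-88% |
| Log ANCOVA | 87-98% | 87-98% |

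An independent rerun agreed to within about one percentage point. Compared scenario by scenario, log ANCOVA gains 1-7 points over raw ANCOVA at log SD 0.3-0.5 and about 9-22 at 0.8-1.0. With mild skew, most of the gap between the first and last rows is therefore due to baseline adjustment and not to the log scale.

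**Step 3: choice among analyses under no effect.** With two time points and two arms, the group-by-time test of the repeated-measures ANOVA is the same as a t-test on change. The three raw-scale tests are then the month-3 t-test, the change t-test and ANCOVA. At least one reaches p < 0.05 in about 7-11% of null trials per outcome. Each test used alone stays near its nominal level: in a companion simulation with 63 per arm, type I error was 0.036-0.048 for every single method, including a rule that tests normality and then picks the t-test or the rank test.

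**The case against.** The strongest reply is that the paragraph already plans a baseline- and centre-adjusted covariance analysis, so the better method is not absent. This stands. A reader might infer from the t-test sentence that baseline adjustment is missing from the plan, and the text does not support that. What remains is that the adjusted analysis is not given precedence over the t-test named for these specific outcomes.

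Four further replies deserve an answer.

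- **Much power lost through skew.** A reader might infer this, but the documents report no distribution for any of these outcomes. A log-normal model with a multiplicative effect favours the log scale by construction, and it does not describe AFC, which is a count. The loss from staying on the raw scale with ANCOVA is small under mild skew. Power of a change-score t-test also depends on whether treatment raises or lowers the outcome, so no such figure is relied on here.
- **Data-driven switch to Mann-Whitney.** That sentence concerns comparability of characteristics; extending it to outcomes is plausible but not stated. If it were extended, the rank test would remove nearly all of the skew penalty (77-80% power in the same setup, against 80% by design for the log t-test), but it would still not adjust for baseline or centre.
- **Repeated-measures ANOVA.** For outcomes measured twice it is redundant, not wrong, and Bonferroni contrasts do exist for CMS at three time points.
- **Detail for an SAP.** Transformations are often left to one, and none is shown, so the absence of a log scale is not in itself a fault. But an SAP would have to override a test that the article names, and competing named analyses are a defect of the stated text.

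**Conclusion.** The point holds as one about an unfixed main analysis with the weaker option named for these outcomes. Under the stated assumptions, following the t-test sentence gives about 73-77% power where raw ANCOVA gives 83-96% (log SD 0.3-0.5), and 59-68% against 67-88% with stronger skew. The loss from ignoring baseline needs no skew, only a baseline correlation of the assumed size.

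The further gain from a log scale is real only to the extent that the data are skewed, which the documents do not show. The 7-11% false-positive rate describes unrestricted choice among three tests. It is not evidence that the sponsor would choose in that way, and no single test is inflated. As these are secondary outcomes without stated power, this is a worthwhile, inexpensive improvement and not a threat to the primary result.

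**What to change.** Before unblinding, replace the independent t-test for the secondary outcomes with one named between-group analysis per outcome:

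- **FSH, LH, E2, AMH:** ANCOVA of the log month-3 value on log baseline and centre, reported as a ratio of geometric means with 95% CI.
- **PSV:** ANCOVA of the untransformed month-3 value on baseline and centre.
- **AFC:** a baseline-adjusted count or ordinal model.

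State that this is the sole between-group analysis of each outcome. Limit the Mann-Whitney sentence to baseline characteristics, and keep the repeated-measures analysis for CMS only, which is measured at months 0, 3 and 6.

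The cost is wording. Sample size, visits and measurements do not change. Two small downsides follow: hormone and AMH results become ratios instead of mean differences, and AMH values below the assay limit need a stated substitution.

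### Three analyses of the primary CMS comparison at p < 0.05, with no statement of which one, or which visit, decides the trial

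*Protocol article*

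**What the plan says.** CMS is the primary outcome. The abstract states that "CMS will be measured before the intervention, at 3 months and 6 months after randomization for all participants". No section labels month 3 or month 6 as the primary time point.

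The Statistical analysis section gives the between-group comparison of CMS three treatments:

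- **Independent t-test.** Differences in CMS and the secondary measures "at month 0 and month 3 between the BSHX and placebo groups will be compared using an independent" t-test.
- **Covariance analysis.** To control centre and baseline effects, "covariance analysis will be applied for the intergroup comparison with continuous variables". This includes CMS. The visit is not stated.
- **Repeated-measures ANOVA.** "A repeated-measures analysis of variance (ANOVA) test with Bonferroni post hoc test will be used to evaluate the changes in CMS scores", the secondary measures and the safety measures across the whole trial.

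Paired t-tests within each arm are also listed. One threshold, p < 0.05, applies to every test, and no order of priority is given.

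The Sample size calculation section sizes the trial on the between-group difference in total CMS before and after treatment. It assumes that BSHX "would reduce CMS score by 2.9 points and the SD is 7.42 in the study".

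**The concern.** The three methods answer nearly the same question and can disagree. A t-test at month 3 may miss significance while the ANCOVA reaches it, or the reverse; the repeated-measures analysis may be significant because of month 6 alone. The text has no rule for such a case, so the deciding p-value could be chosen after the results are seen. That weakens the claim that the trial tests its primary hypothesis at 5%.

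The choice also affects power. The only between-group test tied to CMS at a specific visit is the t-test without covariate adjustment. It is less efficient than the ANCOVA listed beside it, although baseline CMS is collected from everyone.

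**Working it through.** **The plan's own figure.** The printed formula is n per group = 2 × [(z(1−α/2) + z(1−β)) × σ/δ]², with σ = 7.42 and δ = 2.9, so σ/δ = 2.5586.

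- Two-sided, 90% power: 2 × [(1.96 + 1.28) × 2.5586]² = 137.4, so 138 per group.
- With the one-sided quantile that the text prints ("1.64, u1 − *β* =1.28"): 2 × [(1.64 + 1.28) × 2.5586]² = 111.6, so 112 (113 with unrounded quantiles).
- Two-sided without the leading factor 2: 68.7, so 69.

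The stated 70 per group is reproduced only by the last version. This is a separate matter, but it means that two-sided power is well below 90% and the primary method matters more.

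**Inputs for the check.** Recruitment is 150 with up to 15% loss: 150 × 0.85 / 2 = 63.75, about 64 per arm. The correlation between CMS visits is not in the document. I assume r = 0.3, 0.5 and 0.7, equal between all pairs of visits. The document does not say whether 7.42 is the SD of the score or of the change, so both are shown.

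**False-positive chance if any positive result may be claimed.** Null trials were simulated with baseline, month 3 and month 6 (10,000 per correlation, 70 per arm):

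| Set of tests, two-sided 0.05 | r = 0.3 | r = 0.5 | r = 0.7 |
|---|---|---|---|
| ANCOVA at month 3 alone | 5.1% | 4.8% | 5.0% |
| t-test on month-3 scores, or ANCOVA | 6.5% | 7.2% | 8.2% |
| the same, or repeated-measures interaction | 9.9% | 10.5% | 11.0% |
| t-test on change, or ANCOVA | 7.8% | 7.2% | 6.9% |
| the same, or repeated-measures interaction | 10.2% | 9.7% | 9.1% |

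A rerun with 64 per arm gave practically the same results. Treating three tests as independent would give 1 − 0.95³ = 14.3%. That overstates the risk, because the tests are correlated.

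**Power for 2.9 points, two-sided 0.05, 64 per arm.**

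- t-test: SE = 7.42 × √(2/64) = 1.312; 2.9/1.312 = 2.21; power 59% (noncentral t; the normal approximation gives 60%). This is the test on month-3 scores if 7.42 is the SD of the score, and the test on change if it is the SD of the change.
- ANCOVA, 7.42 as SD of the score: residual SD = 7.42 × √(1 − r²) = 7.08, 6.43 and 5.30; power 63%, 72% and 87%.
- ANCOVA, 7.42 as SD of the change: score SD = 7.42/√(2(1 − r)); residual SD = that × √(1 − r²) = 5.98, 6.43 and 6.84; power 78%, 72% and 66%.

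Under both readings ANCOVA has more power than the t-test that corresponds to the quoted SD, by about 4 to 28 points under the first and 19 down to 7 points under the second.

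**The case against.** The strongest reply is that this is a condensed article, and that ranking listed analyses is often left to a statistical analysis plan. That would answer silence. Here the text itself sets out competing tests of one primary outcome at one threshold, so the conflict stands in the document.

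Other parts of the reply limit the point, and they hold:

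- **Baseline is not ignored.** A reader might infer that the plan throws away baseline CMS and so wastes power. It does not: ANCOVA for centre and baseline is already listed. The loss attaches to the t-test only if that test decides.
- **The t-test is not planned for month 6.** A reader might spread all three methods over both months. The t-test covers months 0 and 3 only; month 6 enters through the repeated-measures ANOVA. The sample-size text points to month 3.
- **Larger inflation figures need more than the text says.** Counting the t-test both on month-3 scores and on change gives 9 to 10%. Adding the repeated-measures analysis and an ANCOVA at month 6 gives 14 to 15%. The sentence supports one reading of the t-test at a time, and no month-6 ANCOVA is stated.
- **Inflation is conditional.** Nothing says that any positive result may be claimed; nothing excludes it either. The Bonferroni post hoc test covers comparisons inside the ANOVA, not the choice among methods.
- **Paired tests.** The article does not present the within-group tests as proof of efficacy. The caution about them is secondary.
- **Numbers analysed.** Dropouts' last recorded data are to be analysed. At 75 per arm the t-test would have 66% power rather than 59%.

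**Conclusion.** The point holds as a conflict in the stated analysis: three methods for the primary comparison, one threshold, and no deciding method or visit, although month 3 is implied.

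If any positive result could be claimed, the false-positive chance would be about 6.5 to 8% for the month-3 t-test or ANCOVA, and about 10 to 11% with the repeated-measures interaction. One pre-named ANCOVA keeps it at about 5%. These figures rest on normal data, equal visit correlations of 0.3 to 0.7 and complete follow-up.

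The power gain of ANCOVA over the t-test is real, but its size is uncertain. The 87% applies only if 7.42 is the SD of the score and r is 0.7. If 7.42 is the SD of the change, the order reverses and power falls from 78% to 66% as r rises. Neither case should be quoted alone.

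**What to change.** In the Statistical analysis section:

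1. Name one primary analysis: ANCOVA of total CMS at month 3, with treatment, baseline CMS and centre, reporting the adjusted difference with a two-sided 95% confidence interval.
2. Label the independent t-test, the repeated-measures ANOVA and the month-6 results as supportive.
3. Drop any between-group significance test at month 0, which only tests whether randomisation worked.
4. State that within-group paired tests are descriptive and not evidence of efficacy, since placebo response alone can make them significant.

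State month 3 as the primary time point in the Primary outcome section as well, and say in the Sample size calculation section whether 7.42 is the SD of the score or of the change.

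The cost is wording only. Baseline CMS, centre and the covariance analysis are already in the plan, and no new data are needed. The change should be made and dated before unblinding.
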